**General Introduction**

**Childhood pneumonia**

*Mortality*

Childhood pneumonia is the leading single cause of mortality in children age less than 5 years. It is responsible for about 17% of all deaths in children age less than 5 years, of which more than 70% take place in sub-Saharan Africa and South-east Asia. [Black 2010]

*Incidence of clinical pneumonia*

The estimated incidence of pneumonia in young children for developing countries was 0.28 episodes per child-year (interquartile range from 0.21–0.71) based on an analysis of data from selected 28 community-based longitudinal studies). [Rudan 2004]. Estimates of clinical pneumonia incidence are highest in South-East Asia (0.36 episodes per child year), followed by Africa (0.33 episodes per child year) and by the Eastern Mediterranean (0.28 episodes per child year) and lowest in the Western Pacific (0.22 episodes per child year), Americas (0.10 episodes per child year) and Europe (0.06 episodes per child year) [Rudan 2008]. Of all community-based episodes of pneumonia 7–13% are severe enough to be life-threatening and require hospitalization.

*Global Action Plan for the Prevention and Control of Pneumonia (GAPP)*

In response to the Millennium Development Goal 4 (MDG4) challenge of reducing the under-five mortality rate by two-thirds between 1990 and 2015, WHO/UNICEF have developed the Global Action Plan for the prevention and control of Pneumonia (GAPP). GAPP recommends that children be provided with healthy environments and access to preventive interventions to protect them from getting pneumonia and also to access to treatment if they do develop pneumonia. The specific aims of the GAPP are to:

- Reduce mortality due to pneumonia, in children under the age of 5, by 65% by 2015, compared with levels in 2000
- Reduce the incidence of severe pneumonia by 25% in children under the age of 5 by 2015, compared with levels in 2000

To achieve these goals it is necessary that levels of coverage of effective interventions against pneumonia increase rapidly. In order to monitor progress in coverage there is a need for valid measures of coverage. Although UNICEF, USAID and other agencies have invested heavily in efforts to track coverage through the development and implementation of the DHS and Multiple Indicator Cluster Surveys (MICS), as well as working to establish interagency consensus on the most important indicators to track over time, methodological weaknesses in current efforts to measure coverage (and especially coverage trends over time) have been highlighted. Some of these weaknesses are being addressed (e.g. the Institute for Health Metrics and Evaluation reports that they are working on a subset of 30 coverage indicators to improve assessments of “effective coverage”). However, there remains an urgent need to improve the validity and reliability of coverage measurement, across countries and over time.

Of particular importance are coverage indicators of *correct treatment of childhood infectious diseases*, especially those for pneumonia. Prompt treatment with a full course of antibiotics can reduce deaths from pneumonia by over 40%, and strategies to achieve high, sustained and equitable coverage for this intervention are receiving increasing attention. Despite its importance, efforts to measure antibiotic treatment coverage have lagged behind those for other major causes of child deaths. These need to be reassessed in the light of changing clinical guidelines and new efforts to promote community case management of pneumonia. **Two urgent challenges are: (1) to identify the best methods for assessing short-term trends in these indicators, so that the results can be used to improve program approaches and delivery strategies; and (2) to identify methods for assessing and reporting uncertainty.**

**Demographic and Health Surveys (DHS) and Multiple Indicator Cluster Surveys (MICS)**

DHS and MICS are household surveys designed to assess coverage levels which are widely used in developing countries. To gain information about childhood morbidity and treatment practices (in addition to many other health-related data), the primary caregivers of the household are interviewed about their child’s recent health. The interview follows a structured questionnaire in which the mother is questioned about the presence or absence of specific signs and symptoms displayed during their child’s recent illness. The accuracy and reliability of these data has been questioned, in particular in relation to data on childhood pneumonia [Lanata 1994; Harrison 1995; Colham 2000].

Until about 2006, these surveys did not include an indicator on pneumonia treatment – instead a proxy was used based on caregivers’ reports of careseeking for children with cough and fast breathing who did not have a blocked or runny nose. The Phase 5 DHS protocol asks caregivers of children with a cough and fast or difficult breathing (but without a blocked or runny nose) who report giving the child a treatment to identify when treatment was started (days after illness began illness) and an open-ended question about what drugs were given, with prompting (“Any other drugs?”). Surveyors check boxes for “pill/syrup” or “injection” if an antibiotic is reported by the caregiver. We are not aware of any studies that have attempted to assess the validity of responses offered by caregivers to these questions.

There are two major obstacles to overcome in gaining accurate morbidity information about childhood pneumonia from maternal interview. The first problem is that the interview only provides the most likely diagnosis from the recalled signs. Therefore, diseases which have a very distinct set of clinical signs which are easily recognized by the caregiver (such as diarrhoea) are more easily and accurately diagnosed by these methods than those (such as pneumonia) which are more difficult to recognize by caregivers. Secondly, as with all health interview data, there is a significant problem with the recall period. A study conducted in Egypt found that the specificity of many terms fell over time. The choice of recall period for these surveys is a trade-off since it needs to be long enough to include sufficient illness episodes whilst short enough to minimize memory decay. A study to validate the pneumonia algorithm contained within the MEASURE DHS phase III (donated as just “DHS” in this protocol) and MICS surveys has not yet been conducted.

**Project overall aim**

The objective this project is to improve the measurement of reported antibiotic treatment for pneumonia in children 0 to 5 years of age by mothers.

**Project research questions**

- What is the sensitivity and specificity of the MEASURE DHS PHASE III and MICS questionnaires for caregiver recognition of pneumonia (compared to an expert physician gold standard diagnosis)?
- What are the equivalent estimates of sensitivity and specificity when using an amended survey tool which incorporates:
  - a pneumonia score?
  - video illustrations of signs of pneumonia presented to caregivers?
- What is the sensitivity and specificity of the MEASURE DHS PHASE III and MICS questionnaires for caregiver recall of antibiotic treatment in children with and without pneumonia? (compared to an accurate record of treatment made at time of prescription)?
- What are the equivalent estimates of sensitivity and specificity when using an amended survey tool which incorporates:
  - A paper-based “pill/medicine board” illustrating different locally available treatment options
  - A computer based “pill/medicine board” illustrating different locally available treatment options
- Is there a significant difference in the accuracy of caregiver recall of diagnosis or antibiotic treatment between the 2 weeks and 4 weeks follow up protocol?

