**Table 1: Characteristics of the study sites**

| **Pakistan Urban** |  |
| --- | --- |
| *Geographic Location:* | Islamabad |
| *Principal Investigator:* | [name] |
| *Subcontracting Institution:* | Children’s Hospital, Pakistan Institute of Medical Sciences, Islamabad, Pakistan. |
| *Strategy for recruitment of children with pneumonia:* | Pneumonia cases identified at PIMS, a major children’s hospital by a trained doctor |
|  |  |
| **Bangladesh Rural** |  |
| *Geographic Location:* | Four rural villages: Mirzapur, Gorai, Bhatgram, Jamurki |
| *Principal Investigator:* | [name] [name] |
| *Subcontracting Institution:* | ICDDR,B |
| *Strategy for recruitment of children with pneumonia:* | Pneumonia cases identified at local government health services by a trained doctor |

*Recruitment at clinic*

Children aged 0 to 5 years who present to a health clinic or hospital out-patient department suffering from acute respiratory symptoms will be eligible to be recruited into the study. The children will be assessed according to a standard protocol by a study doctor and key clinical and treatment details recorded. A diagnosis of pneumonia, severe pneumonia or of “cough or cold” (no pneumonia) following an agreed clinical classification system and details of all treatment prescribed will be carefully recorded. Children presenting primarily with an episode of recurrent wheeze (reactive airways disorder / asthma) or who have pneumonia severe enough to require hospital admission or who have symptoms of more than 4 weeks duration or who have already received treatment from health services for the current illness episode will be excluded (so as to limit recall bias associated with the admission).

A detailed address will be recorded and consent sought for a follow up visit. The study will aim to recruit and follow up successfully 300 children with pneumonia (or severe pneumonia if this is treated in the community) and 300 with “cough or cold” (no pneumonia) at each study site. An attempt will be made to recruit all children with pneumonia who present during the defined study period when a trained clinical researcher is available. Children with “cough or cold / no pneumonia” will be frequency matched to pneumonia cases so that in any one week the age and sex distribution of cases of pneumonia and “cough or cold” are similar.

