All children will then be treated according to the standard management protocols of that particular clinic. It is expected that some of the study children with pneumonia will go on to develop severe pneumonia, and require hospital referral. If this should happen the local health worker will ensure that the child is referred to the nearest health facility to receive medical care. A detailed record of the treatment given to the caregiver will be recorded.

It is recognized that children attending a clinic with pneumonia could represent a biased group that are not fully representative of all sick children. We will collect DHS data on socio-economic status in order to compare the sample population to a wider population. Furthermore, it is possible that the consent process and information sheet may introduce a source of bias in the recording of recall of symptoms and events.

*Follow up at home*

The primary caregivers of these children will first be interviewed using the DHS and MICS questions relating to pneumonia (see Annex) either at 2 weeks (200 with pneumonia and 200 with cough or cold) or 4 weeks (100 with pneumonia and 100 with cough or cold) after diagnosis. This will follow the DHS and MICS procedures as closely as possible. The order of administering the DHS and MICS questionnaires will be alternated with each child so that each is administered first on 50% of occasions. After this is completed they will then also be questioned about specific signs of pneumonia (which will form a pneumonia score - see below) and will be asked to watch a video of a child suffering from pneumonia and of a child suffering from an upper respiratory infection (asking which best represents their child’ respiratory illness episode). Finally, a drug chart will then be used to show them pictures of locally used medicines with a request to identify which medicines, if any, their child was prescribed. These research workers should be given the address details of the child but not be made aware of the study group of the child nor have access to the clinical details of the child recorded at recruitment.

*Home visit interview sequence:* The research worker will

1. introduce him/herself to the caregiver, and check that the details match those on the recruitment form.
2. inform the mother of the interview process and ensure that she is willing to participate (and obtain written consent).

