***This same table will be used for the MICS diagnosis**

|  | | **Medical diagnosis of Pneumonia** | | |
| --- | --- | --- | --- | --- |
|  | | **+ve** | **-ve** | **Total** |
| **Does child reach specific pneumonia score (e.g. 5)** | **Y** | **a** | **B** | **a+b** |
| **N** | **c** | **D** | **c+d** |
| **Total** | **a+c** | **b+d** | **n** |

|  | | **Medical diagnosis of Pneumonia** | | |
| --- | --- | --- | --- | --- |
|  | | **+ve** | **-ve** | **Total** |
| **diagnosis of pneumonia**  **from video** | **+ve** | **a** | **B** | **a+b** |
| **-ve** | **c** | **D** | **c+d** |
| **Total** | **a+c** | **b+d** | **n** |

- Sensitivity = a/(a+c)
- Specificity = d/(d+b)

We will use Receiver operating characteristic (ROC) curves to present the results of the pneumonia score to determine the most appropriate score threshold.

We will also assess the validity of the report of treatment received in the same way.

|  | | **Child received drugX*** | | |
| --- | --- | --- | --- | --- |
|  | | **Y** | **N** | **Total** |
| **Mother said child received drugX*** | **Y** | **a** | **B** | **a+b** |
| **N** | **c** | **D** | **c+d** |
| **Total** | **a+c** | **b+d** | **n** |

*Drug X will be substituted for each of the medications listed

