During the interview, the research worker will show the caregiver a chart which will contain pictures of all the locally used medications. The research worker will ask the caregiver which, if any, of these treatments her child received. This drug chart should be presented both as a separate laminated sheet and loaded onto the study laptop PC to be displayed after the video is shown. The drugs shown should be clearly displayed, with any identifying marks (e.g. markings) easily visible. The caregiver will also be asked about details of dose and duration of treatment given and source of the medication. The pilot study will consider methods proposed in the WHO manual edited by Hardon before the final study protocol is established.

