2. *How many days after the illness began did you first seek advice or treatment for (NAME)? If the same day, record ‘00’.*
3. *Is (NAME) still sick with (fever/cough)?*

*Fever Only 1*

*Cough Only 2*

*Both Fever and Cough 3*

*No, Neither 4*

*Don’t Know 5*

1. *At any time during the illness, did (NAME) take any drugs for the illness?*

*Yes 1*

*No 2*

1. *What drugs did (NAME) take? Any other drugs? Record all mentioned.*

*Antimalarial Drugs*

*SP/Fansidar A*

*Chloroquine B*

*Amodiaquine C*

*Quinine D*

*Combination with Artemisinin E*

*Country Spec. CBD Antimalarial F*

*Other Antimalarial G*

*________________ (specify)*

*Antibiotic Drugs*

*Pill/Syrup H*

*Injection I*

*Other Drugs*

*Aspirin J*

*Acetaminophen K*

*Ibuprofen L*

*Other ________________ (specify) X*

*Don’t Know Z*

*Followed by specific questions about each drug mentioned…*

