**Annex 4:** **DRAFT** **Form to be completed by Physician**

Section 1: patient details

Child’s Name (full): ………………………………………........................................

Age: …………………………………………………………………………………...

D.O.B: ………………………………………………………………………………...

Mother’s/

primary caregiver’s name: ………………………………………………......................

Address: ……………………..................

……………………..................

……………………..................

……………………..................

……………………..................

Date of examination:………………………………………………………………....

Section 2: presenting signs + symptoms

Respiratory symptoms: ……………………………………………………………...

……………………………………………………………..

……………………………………………………………..

Respiratory rate:

Temperature (oC):

Sub-costal retractions / lower chest wall indrawing (y/n):

Record any findings on auscultation -

Section 3: Investigation

Chest X-ray ordered (y/n):

Section 4: Diagnosis

Pneumonia non-pneumonia (circle appropriate)

Presence of exclusion criteria

- - recurrent wheezing
  - chronic cough (more than 10 days)
  - already on antibiotic treatment
  - recent pneumonia episode within past 10 days
  - history of congenital heart disease
  - symptoms for more than 4 weeks
  - previous clinic treatment for this illness episode

Section 5: Treatment (to be adapted for each site)

| *Drugs* | | *Please tick those prescribed* |
| --- | --- | --- |
| *Antimalarial Drugs* | *SP/Fansidar* |  |
|  | *Chloroquine* |  |
|  | *Amodiaquine* |  |
|  | *Quinine* |  |
|  | *Combination with Artemisinin* |  |
|  | *Country Spec. CBD Antimalarial* |  |
|  | *Other Antimalarial* | **Specify:** |
|  |  |  |
| Antibiotic Drugs | *Pill/Syrup* |  |
|  | *Injection* |  |
|  |  |  |
| Other Drugs | *Aspirin* |  |
|  | *Acetaminophen* |  |
|  | *Ibuprofen* |  |
|  | *Other* | **Specify:** |

Physician name:………………………………..

Date:……………………………………………

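### Treatment recall is scored against what the clinic prescribed, but DHS/MICS ask what the child took or was given, and the drug-chart question is worded both ways

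*Protocol*

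**What the plan says.** **Reference.** The third item under Project research questions sets caregiver recall of antibiotics against a clinic record: "compared to an accurate record of treatment made at time of prescription". Recruitment at clinic says that "details of all treatment prescribed will be carefully recorded", and the treatment section of the draft physician form (Annex 4) is headed "Please tick those prescribed". One sentence, just before Follow up at home, differs: "A detailed record of the treatment given to the caregiver will be recorded". That could mean dispensing.

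**Caregiver items.** The DHS item in Annex 1 asks, for any time in the illness, "did (NAME) take any drugs for the illness". Annex 1 says its questions will be replaced by a later DHS version that is not shown. MICS item CA12 (Annex 2) asks whether the child was given medicine for the illness. Neither is restricted to the clinic visit.

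**Drug chart.** Follow up at home presents the chart "with a request to identify which medicines, if any, their child was prescribed". Step 7 of the home visit sequence asks with what the child was treated. The Drug Chart note says: "The research worker will ask the caregiver which, if any, of these treatments her child received".

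**Scoring.** In the treatment two-by-two table the row is "Mother said child received drugX", and the reference column is likewise labelled as the drug the child received. The indicator in Study rationale is also about receipt.

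**The concern.** Prescription and intake are different facts. A prescribed antibiotic may not be obtained or not be given, and a child prescribed none may get one elsewhere after the visit. DHS and MICS ask about intake, so a caregiver who answers truthfully in the first case becomes a false negative and in the second a false positive. The table's column label hides this, because no reference measure of receipt is specified.

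Two results are at stake. One is the absolute sensitivity and specificity of DHS/MICS for antibiotic treatment, the project's main subject. The other is the comparison of the picture chart with DHS/MICS. If the chart asks about prescription while DHS/MICS ask about intake, only the chart's question matches the reference, and it can look better for that reason alone.

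**Working it through.** The plan states no figure for this discordance, so there is nothing to reproduce. The check has two parts.

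**1. Wording side by side**

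| Place in the protocol | Fact referred to |
|---|---|
| Project research questions (reference) | prescribed |
| Recruitment at clinic (reference) | prescribed |
| Annex 4, Section 5 (reference, draft) | prescribed |
| Sentence before Follow up at home (reference) | given to the caregiver |
| Treatment two-by-two table, reference column | received by the child |
| DHS, Annex 1 (placeholder) | taken by the child |
| MICS, CA12 | given to the child |
| Chart, Follow up at home | prescribed |
| Chart, interview step 7 | treated with |
| Chart, Drug Chart note | received |

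The reference and the survey items do not target the same fact, and the chart question takes both sides.

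**2. Size of the effect**

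Let a be the share of prescribed antibiotics not given, b the share of children not prescribed an antibiotic who get one elsewhere, and Se and Sp the true accuracy of recall of intake. Recall errors are assumed to depend only on intake. Scored against the prescription:

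- apparent sensitivity = (1 − a)·Se + a·(1 − Sp)
- apparent specificity = (1 − b)·Sp + b·(1 − Se)

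Both fall by the discordance multiplied by (Se + Sp − 1). The values of a, b, Se and Sp are assumptions. The last two rows use pairs within the ranges in Sample size calculation (sensitivity 60–70%, specificity 70–90%).

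| True Se / Sp | 5% discordance | 10% | 20% |
|---|---|---|---|
| 100 / 100 | 95 / 95 | 90 / 90 | 80 / 80 |
| 90 / 90 | 86 / 86 | 82 / 82 | 74 / 74 |
| 70 / 90 | 67 / 87 | 64 / 84 | 58 / 78 |
| 60 / 70 | 58.5 / 68.5 | 57 / 67 | 54 / 64 |

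Worked example, 90/90 at 10%: 0.90 × 0.90 + 0.10 × 0.10 = 0.81 + 0.01 = 0.82.

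The bias reaches the ±5-point precision target when discordance = 0.05/(Se + Sp − 1): 0.05/0.80 = 6.3% at 90/90, 0.05/0.60 = 8.3% at 70/90, and 0.05/0.30 = 16.7% at 60/70. A larger sample does not shrink it.

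**Chart against DHS/MICS.** Suppose that the pictures add nothing, that recall is 90/90 for whichever fact is asked, and that discordance is 10%. A chart asking about prescription scores 90% and DHS/MICS score 82%. The apparent gain of 8 points comes entirely from the changed question.

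**The case against.** Several points on the other side stand.

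- **The comparator is declared.** The research question says openly that the reference is the prescription record. Agreement with that record is a legitimate quantity, but the table labels it as receipt.
- **Dispensing.** If the record of treatment given to the caregiver means drugs handed over, error from unfilled prescriptions largely goes. Non-administration and later treatment from elsewhere remain.
- **Safeguards.** Children already treated by health services for the episode are excluded, so the problem is mainly what happens after the visit. Source of medication, medicines seen in the home and pharmacist's notes are collected. The protocol does not say that they alter the reference or the scoring. A SAP might, but the meaning of the reference is a protocol matter.
- **DHS wording.** Annex 1 is a placeholder. The MICS wording, which carries no such notice, shows the same mismatch.

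Three stronger readings are tempting and not supported.

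- A reader might set the bias against the 10-point difference in Sample size calculation. That figure concerns 2-week versus 4-week recall. With equal discordance in both groups most of the bias cancels: at 10% not given, a true 10-point sensitivity difference appears as 0.9 × 10 = 9 points, or 9 − 0.1 × 10 = 8 if specificity also falls by 10.
- A reader might infer that the expected hospital referrals create many false positives. Those are children with pneumonia. Any who were prescribed an antibiotic at the index visit are already reference-positive, so a hospital antibiotic could mislead only in a drug-by-drug table.
- A reader might conclude from the generic antibiotic rows in Annex 4 that the reference cannot support a per-drug table. The form is marked as a draft, and its treatment section is to be adapted by site.

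**Conclusion.** The point holds as a mismatch between reference and question, together with a contradiction in the chart wording. It does not mean that truthful answers are generally scored as errors: that happens only where prescription and intake differ, and the documents do not say how often.

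Under the assumed inputs, 10% discordance lowers absolute sensitivity and specificity by 3 points (60/70), 6 points (70/90) or 8 points (90/90), against a ±5-point target. The downward direction requires Se + Sp above 1 and caregivers who answer the question as worded. Those who report the clinic's prescription whatever was asked would reduce the bias. The 2-week versus 4-week contrast is little affected if discordance is similar in both groups. The chart comparison is confounded in this way only if the Follow up at home wording is the one fielded. This should be settled before the forms are final.

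**What to change.** 1. **Chart question.** Change Follow up at home so that the chart asks what the child received for this illness, in line with DHS/MICS, interview step 7 and the Drug Chart note. Moving the chart to prescription instead would fix the confounding in place and take the chart away from the receipt indicator.
2. **Reference.** Decide whether the clinic record is of drugs prescribed or dispensed, and make Project research questions, Recruitment at clinic, the sentence before Follow up at home, and Annex 4 agree. Relabel the reference column as prescribed (or dispensed) at the index visit, and describe the estimates as agreement with that record.
3. **Supportive analysis.** After interview step 8, where it cannot influence earlier answers, add one item on whether each prescribed medicine was given. Use it with the source of medication, home observation and pharmacist's notes to set aside or reclassify antibiotics not given or obtained elsewhere, and report the results beside the main ones.

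The cost is rewording and one extra question, with the standard DHS and MICS items untouched. The supportive analysis rests partly on the same caregiver's report, so it is not independent of the answers being tested and should not replace the main one.
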